### Recruitment and Eligibility Criteria

Following ethics approval, we will contact EP and physiotherapy practices in the Greater Brisbane region through Federal Government (DVA) and professional organization (Exercise and Sports Science Australia and Australian Physiotherapy Association) communication networks (eg, newsletters and social media) to inform them of the trial. EPs and physiotherapists interested in offering the program to their clients will act as “gatekeepers” for study recruitment. They will apply study inclusion criteria to DVA-funded clients and link eligible and interested clients with the study team for provision of informed consent. Eligibility criteria will be assessed a second time when obtaining informed consent from participants.

To be included in the study, participants must be ADF veterans and their dependents who are eligible to receive DVA-funded allied health treatment from an EP or physiotherapist, ≥50 years of age (this is based on recent data showing that 80% of the DVA treatment population are over 50 years old, with an average age of 67.25 years) [4], and identified by their treating EP or physiotherapist as able to safely transition from supervised treatment to self-managed PA. The DVA client population includes both ADF veterans and other eligible recipients of DVA-funded healthcare, mostly widow/ers of ADF veterans whose death was determined to be related to their military service.

Participants will be excluded if they are (1) under medical management for complex or chronic conditions that require supervised treatment from a health professional (inclusive of spinal cord injury, brain injury, severe mental health problems, chronic pain, stroke, amputations, and complicated orthopedic injury), (2) currently participating in another DVA-funded PA program, and (3) current serving ADF personnel.

### Interventions

#### Active Choices Program

Participants attending EP or physiotherapy practices allocated to the Active Choices intervention group will receive a 12-week program consisting of two 1-hour face-to-face consultations (held in Weeks 1 and 12) and two 30-minute telephone consultations (held in Weeks 4 and 8), which participants will complete individually with an Active Choices consultant.

The program is based on the COM-B Framework [13] and incorporates evidence-based behavior change strategies to support participants’ transition to self-managed PA. These strategies comprise education, goal setting, goal review, self-monitoring, social support, action planning, barrier identification, and problem solving. Strategy selection was also informed by the findings of a systematic review completed by the research team, which identified those utilized in previous intervention studies associated with increased self-managed PA among military service veterans [14].

During consultations held in Weeks 1, 4, and 8, participants will create their individualized Active Choices program, with the support of a consultant, for the proceeding 4 weeks; consistent with our sample size calculations and main outcome measure, focus will be on encouraging weekly activities that elicit self-managed moderate intensity PA equivalent to the recommended guidelines of 150 minutes/week [12], although lighter and more vigorous intensity activities will also be options clients can include in their program where appropriate. This will involve identifying PA preferences and linking participants to preferred activities in their local community, setting PA goals, developing a PA action plan, identifying barriers to PA, and problem-solving solutions to overcome these. Participants will also be actively linked to other participants in their area to facilitate the formation of PA social groups. In addition to these program elements, education about PA will be delivered to participants in Week 1, and a review of previously set PA goals will be conducted in Weeks 4 and 8. At the final consultation in Week 12, participants will review their progress throughout the program and develop a plan for continuing to self-manage PA.

Consultations will be guided by a resource booklet that contains educational and behavioral support materials that map to the behavior change strategies. This booklet will also be used by participants throughout the 12-week program as an educational resource and to self-monitor their PA. A sample of this booklet is provided in Multimedia Appendix 1. SMS reminders will be sent to participants the day before their PA choices in Weeks 2, 5, and 9 as a behavioral prompt.

#### Comparison Program

As Figure 1 describes, participants attending EP or physiotherapy practices allocated to the comparison group will receive a 12-week program that is more self-directed, has fewer consultation sessions, and incorporates fewer behavioral support strategies than the Active Choices program (ie, education, self-monitoring, and action planning only). The comparison program consists of two 1-hour face-to-face consultations (held in Weeks 1 and 12) that participants will complete individually with an Active Choices consultant. During the consultation in Week 1, participants will receive education about PA and identify their PA preferences. They will also be given materials to help them identify local opportunities for their PA choices and to develop their PA action plan independently at home. At the consultation in Week 12, participants will reflect on their progress during the past 12 weeks and identify their PA action plan for continuing to self-manage PA. Consultations will be guided by a resource booklet, and participants will use this booklet to self-monitor their PA across the 12-week program.

#### Concomitant Care

Involvement in the research will not replace existing treatment plans but seek to “value-add” scaffolding for behavioral support that can benefit clients and the PA specialist. Therefore, participants in practices allocated to both programs will continue to have the option of accessing allied health treatment from their EP or physiotherapist during the 24-week study period.

### Outcome Measures

#### Overview

The primary outcome of self-managed moderate intensity PA and secondary outcomes of psychological well-being and social connectedness will be assessed at baseline, end-intervention (Week 12), and follow-up (Week 24; see Figure 1). In addition, physical measurements of height and weight and a lifestyle survey assessing quality of life and health behaviors (nutrition, smoking, and alcohol use) will be completed at these time points. Standard demographic items assessing age, gender, education, employment, and household status will be administered at baseline.

Measures will be administered by trained researchers and standardized with calibration of devices and equipment prior to measurement sessions. An Aus $50 (US $38.71) grocery voucher will be offered to incentivize participants to complete follow-up measures at 24 weeks.

#### Primary Outcome Measure

The primary outcome measure of Active Choices is moderate intensity self-managed PA (equivalent to recommended guidelines of 150 minutes/week [12]) assessed by accelerometer devices. Accelerometers are now widely recognized as an affordable, practical, and highly accurate means of assessing PA [15]. We will use a triaxial accelerometer (wGT3X+, ActiGraph, Pensacola, FL) to assess PA using the same protocol at the 3 measurement time points. Participants will wear the device on their nondominant wrist for 7 consecutive days (24 hours) and keep a diary to record times when they attended treatment with their EP or physiotherapist, when the device was removed, and sleep hours. Upon return, the raw data from the device will be downloaded and processed. The 24-hour wear-time protocol will record raw acceleration and will be used to quantify overall time in moderate PA (inclusive of land and water-based activities), as well as time spent in light and vigorous intensity activities, sedentary behavior, and sleep. Moderate intensity self-managed PA will be calculated as the difference between total moderate intensity PA minus supervised PA performed during treatment (recorded in the diary).

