## Introduction

The numerous health and psychosocial benefits that accrue through regular participation in physical activity (PA) are well established [1]. PA is particularly beneficial for older people (≥65 years) and plays an important role in retaining independence and life quality through promoting functional fitness, cognitive function, psychological health and well-being, and social connectivity [2].

While active aging can help maintain holistic health and prevent disease, general practitioners are increasingly referring older patients to PA specialists for the treatment and management of existing health conditions, such as high blood pressure, diabetes, or musculoskeletal issues [3]. In Australia, for example, where referrals to exercise physiologists (EP) and physiotherapists may be government-funded, there has been significant growth in the provision of allied health services to older people. Data from the Department of Veterans’ Affairs (DVA), the Australian Government department that provides support to Australian Defence Force (ADF) veterans and their dependents, many of whom are older adults, indicate that from the period of 2011/2012 to 2016/2017, there was a 51% increase in the number of funded services accessed by DVA clients. This was despite a 19% reduction in the number of DVA clients who were eligible to access allied health services [4]. Service uptake was significantly underpinned by large increases in the number of DVA clients who saw an EP or physiotherapist for treatments involving PA.

The benefits of referral to a PA specialist include receipt of expert care and tailored PA guidance during treatment. However, it has been argued that PA referral programs lack behavior change components that promote longer-term adherence [5]. Consequently, such programs do not enable or create channels for patients to “step-down” to self-managed PA after a course of allied health treatment. A stepped-down program is one in which patients transition from allied health care to self-managed behavior [6]. Thus, individuals take responsibility for initiating and maintaining their own PA regimes, instead of being dependent on supervision from a PA specialist.

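### The primary outcome subtracts only diary-logged treatment with the participant's EP or physiotherapist, so another DVA-funded PA program or other EP- or physiotherapist-supervised sessions joined after baseline would count as self-managed PA

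*Protocol article*

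**What the plan says.** Under Primary Outcome Measure, participants wear the accelerometer for 7 days at each of the three time points and "keep a diary to record times when they attended treatment with their EP or physiotherapist, when the device was removed, and sleep hours". The derivation is then fixed: "Moderate intensity self-managed PA will be calculated as the difference between total moderate intensity PA minus supervised PA performed during treatment (recorded in the diary".

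The Introduction gives the meaning of the construct: "individuals take responsibility for initiating and maintaining their own PA regimes, instead of being dependent on supervision from a PA specialist".

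Under Recruitment and Eligibility Criteria, people "currently participating in another DVA-funded PA program" are excluded. Eligibility is applied by the practice at recruitment and checked again at consent. Under Concomitant Care, participants in both arms "will continue to have the option of accessing allied health treatment from their EP or physiotherapist during the 24-week study period". That section does not mention other supervised programs.

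The arms differ in how participants reach local activity. Active Choices consultations include "identifying PA preferences and linking participants to preferred activities in their local community". Comparison participants are "given materials to help them identify local opportunities for their PA choices and to develop their PA action plan independently at home".

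**The concern.** The eligibility criteria show that the investigators regard another DVA-funded PA program as incompatible with the trial at entry. Nothing in the article logs or subtracts such a program if it starts later. A participant who joins one between baseline and Week 24, or who attends sessions supervised by an EP or physiotherapist other than their own, has those moderate minutes left in the primary outcome. The measured quantity is then wider than the stated construct.

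Two estimates are exposed. Data Analyses promises within-group as well as between-group changes. Because the entry criterion sets participation in other DVA-funded programs at about zero at baseline, later uptake can only raise the measured within-group change. The between-group difference is affected only if uptake, or minutes per user, differs between the arms. In either case, some of what is reported as stepping down could be a move from one supervised service to another.

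**Working it through.** **1. What is logged, what is subtracted, what is meant.**

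- Logged: attendance at treatment with the participant's EP or physiotherapist, device removal and sleep.
- Subtracted: supervised PA during that treatment, as logged.
- Meant (Introduction): activity that does not depend on supervision from a PA specialist.
- Barred: another DVA-funded PA program, at entry only.

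The remainder that is neither barred, logged nor subtracted is (a) another DVA-funded PA program joined after baseline and (b) sessions supervised by an EP or physiotherapist who is not read as the participant's own.

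**2. Could other planned data recover it?** The resource booklet records frequency, quantity and types of PA, but only over the 12-week intervention, while the sample size rests on change to 24 weeks. Interviews take place at end-intervention and follow-up. DVA service data are deidentified, need custodian approval and are intended for utilization and costs. These sources might reveal uptake. None enters the outcome derivation, and none is said to give session times that could be matched to the accelerometer record. Times not collected in the wear week cannot be reconstructed at analysis.

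**3. The plan's own figure, to fix the scale.** Inputs from Sample Size: difference 11 min/day, SD 12.7 min/day, power 80%, significance level 5% (taken as two-sided; the article does not say).

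n per group = 2 × (1.96 + 0.842)² × 12.7² / 11² = 2 × 7.85 × 161.29 / 121 = 20.9, so 21 per group and 42 in total, as stated; power is 80.1%. The standard error of the difference at 21 per group, ignoring clustering, is 12.7 × √(2/21) = 3.9 min/day.

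**4. Size of a possible bias.** The documents give no amount or frequency for such sessions, so every input here is an assumption. Let m be unlogged moderate minutes per week per user and d the between-arm difference in the share of users. Bias = (m / 7) × d.

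- Per user: 30/7 = 4.3 and 45/7 = 6.4 min/day.
- m = 30, d = 0.10: 4.29 × 0.10 = 0.43 min/day, 4% of 11.
- m = 45, d = 0.30: 6.43 × 0.30 = 1.93 min/day, 18% of 11.
- d = 0: bias zero for any m, given equal minutes per user.
- If the comparison arm had the higher uptake, the sign would reverse.

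The same product, with d replaced by the share of users within one arm, gives the inflation of that arm's change: 10% to 30% users would add 0.4 to 1.9 min/day.

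**5. What that does to the test.** A bias of 1.93 is 1.93/3.9 = about half a standard error. With no true difference and 21 per group, the two-sided rejection rate is 5.1% at a bias of 0.43, 5.9% at 1.07 and 8.5% at 2.14 min/day, the last just above the range used here. More extreme assumptions give more: 60 minutes per week with a 50-point difference gives 60/7 × 0.50 = 4.3 min/day (39% of 11) and a rejection rate of 19.4%. Nothing in the article makes that likely.

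**The case against.** The strongest reply is that the outcome already matches the aim. The trial concerns leaving EP or physiotherapist treatment, and that treatment is what is subtracted. Someone who chooses and joins an activity is arguably starting and maintaining their own regime even if a leader is present. This stands in part. It rules out calling the outcome rule a contradiction of the Introduction, and it means ordinary led classes in the community should not be subtracted. It does not cover a further DVA-funded PA program, which the eligibility criteria themselves set apart.

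A second reply is that a new treating EP or physiotherapist is naturally the participant's own as well. That reading narrows the gap, but the diary wording leaves participants to decide it.

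Third, an article condenses the full protocol, and the diary form may be wider. That would excuse silence. Here the article states both the diary content and the subtraction rule, so the comment is on what is written.

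A reader might go further and infer that the misclassification favors Active Choices, because its consultants actively link participants to local activity. The documents do not support this. Nowhere are the linked activities said to be DVA-funded or specialist-led, raising community activity is the intended effect, and comparison participants are also pointed to local opportunities. One could equally argue that less-supported comparison participants would seek another specialist. Nor is there support for saying that the cost analysis is distorted: it draws on DVA service data, not on the diary.

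**Conclusion.** The point holds as a gap between a stated outcome rule and the stated construct. Another DVA-funded PA program, or other EP- or physiotherapist-supervised sessions, joined after baseline would be counted as self-managed PA. This can inflate within-group change, and it would bias the between-group difference if uptake differs by arm. The direction and size of any arm difference are not established. Under the assumed inputs the bias is 0.4 to 1.9 min/day, 4% to 18% of the 11 min/day target, and zero with equal uptake. The documents do not say how often such uptake would occur. This is a cheap improvement to make before recruitment, which the Results section says had not begun, and not a flaw that invalidates the design.

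**What to change.** At all three 7-day wear periods and in both arms, extend the diary to the start and end times of any PA session that is supervised by any EP or physiotherapist or delivered as part of another DVA-funded PA program. Subtract the accelerometer-measured moderate minutes within those intervals. State explicitly that client-chosen community activities, including ordinary led classes, stay in the outcome; a broader rule covering anything led by an instructor could remove the behavior the program aims to raise. At Weeks 12 and 24, record by arm whether another DVA-funded PA program has been joined, so that any difference in uptake can be seen.

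The cost is one broader diary entry and one survey item at visits already planned, with slightly more recording for participants. Treatment and access to care are unchanged.

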#### Secondary Outcome Measures

Psychological well-being will be assessed using the Satisfaction with Life Scale [16]*.* This is a widely used, validated instrument that is comprised of 5 items. Responses to each item are made using a 7-point Likert scale (1 = strongly disagree; 7 = strongly agree).

Social connectedness will be assessed using the New Group Membership Scale (NGMS), Social Identity Mapping, and Three-Item Loneliness Scale. The NGMS is comprised of 4 items that assess the extent to which people have joined new social groups and has strong internal reliability [17]. Responses are rated using a 7-point Likert scale (1 = strongly disagree; 7 = strongly agree). The NGMS will be used to determine whether engagement in PA provides a platform to extend people’s social networks to impact on inclusivity. Social Identity Mapping is a validated online tool of social connectedness assessing the multidimensional and connected nature of people’s social group networks (eg, family, work, arts-based, sports) and associated social identities (eg, as a veteran, member of a cycling club, or yoga class). Its elements—that comprise group importance, support, positivity, representativeness, and compatibility—are recognized predictors of a range of health and well-being outcomes. This project will use the latest online version validated in 5 studies [18]. The Three-Item Loneliness Scale is a validated and reliable measure of loneliness and social isolation. It is comprised of 3 items, with responses made using a 3-point scale (1 = hardly ever; 2 = some of the time; 3 = often) [19].

### Process and Qualitative Measures

Self-report data logged by participants in the resource booklet will capture the frequency, quantity, and types of PA participants in both groups engaged with during the 12-week intervention. We will also conduct interviews with participants in both groups at end-intervention and follow-up to explore the extent to which program experiences promoted social connectedness and veteran social networks, aspects of the program that clients found beneficial and enjoyed, and aspects that could be further developed to improve program efficacy.

### Health Service Data

In addition to the measures that will be administered through the trial, we will also seek DVA data custodian approval to access participants’ deidentified health service data. We will use these data to assess treatment history prior to recruitment and health service utilization and costs to the DVA for providing these services during the intervention and follow-up period. This will enable us to determine the cost consequences of the program.

### Data Analyses

Baseline descriptive statistics will be used to summarize the demographic, physical, and lifestyle behavior characteristics of participants, and data will be checked for parametric assumptions. Intention-to-treat analyses will be conducted using linear mixed effects models. This approach will be used to account for the repeated outcome measures over time and the clustered design of the study and will provide estimates on the within-group and between-group changes in accelerometer-measured moderate intensity PA, psychological well-being, and social connectedness. Sensitivity analyses will be conducted to assess the robustness of findings, and for exploratory purposes, subgroup analyses will be performed by gender, age group, and treatment history. The results of all comparative analyses will be presented with 95% confidence intervals, and statistical significance for main effects will be assessed at the 5% level. Statistical analyses will be conducted using Stata (v15; StataCorp LLC, College Station, TX).

To analyze cost consequences, we will determine the costs of Active Choices and of normal treatment alone, inclusive of both the direct costs of implementing the intervention and the implied cost to the DVA (such as the higher or lower utilization of EP or physiotherapist services relative to group allocation). Difference-in-difference analysis will be used to determine whether Active Choices contributes to cost savings, due to a possible reduction in service utilization.

Consistent with recognized guidelines for qualitative data analyses [20], members of our research team will thematically analyze and independently review interview data and discuss the range of responses to agree on key themes. We will use this qualitative approach to triangulate our findings from the statistical analyses (eg, the impacts of the program on self-managed PA) and determine the factors that encouraged or discouraged engagement with the Active Choices program.

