## Methods

### Study Design and Setting

The study is a 24-week, parallel-group, randomized trial for DVA clients (ADF veterans and their dependents) who have been cleared by their treating EP or physiotherapist as able to safely transition to self-managed PA. EP or physiotherapist practices that we engage to recruit eligible participants will be randomly assigned to the Active Choices or comparison program, using an allocation ratio of 1:1.

Randomization will be performed using a simple randomization procedure, based on a computer-generated sequence. Allocation of practices will be concealed at the time of assignment, and members of the research team who will analyze the study data will be blinded to allocation. However, blinding of participants and those who will administer the interventions and outcome assessments will not be possible due to the nature of the program.

Data will be collected from participants at 3 timepoints: baseline, end-intervention (Week 12), and follow-up (Week 24). The trial will be conducted in Brisbane, Australia. Intervention delivery and data collection will take place at the allied health practice the participant attends. A flow chart of the trial is shown in Figure 1.

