### Sample Size

The reference parameters used to calculate the sample size were based on a recent large-scale survey conducted by our team, which examined accelerometer-measured PA in nearly 700 adults living in Brisbane, Australia. This study found participants accumulated an average of 10 minutes/day (70 minutes/week) of at least moderate intensity PA [11]. For our study, sample size was calculated based on change in accelerometer-measured PA, from baseline to 24 weeks, between the 2 groups, in order to detect a minimum average increase of 11 minutes/day (77 minutes/week) of moderate intensity PA. In addition to the PA observed in our reference study [11], this is equivalent to the minimum amount required to achieve standard Australian PA recommendations of 150 minutes/week of moderate intensity PA [12]. Assuming an average of 10 minutes/day (standard deviation of 12.7 minutes/day) at baseline, power of 80%, and significance level of 5%, our power analysis determined that a minimum sample size of 42 (21 in each group) is needed to detect a minimum average increase of 11 minutes/day in moderate intensity PA. To allow for 20% loss to follow-up and 10% noncompliance with PA device use, 52 participants will be recruited to the study (26 in each group).

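### The 5% test is attached to main effects rather than to the week-24 between-group change that sets the sample size, and baseline adjustment of that contrast would add precision at no cost

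*Protocol article*

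**What the plan says.** The Sample Size section defines the powered quantity: "sample size was calculated based on change in accelerometer-measured PA, from baseline to 24 weeks, between the 2 groups". The aim is to "detect a minimum average increase of 11 minutes/day (77 minutes/week) of moderate intensity PA", and the conclusion is that a "minimum sample size of 42 (21 in each group) is needed".

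The Outcome Measures overview has the primary outcome measured at baseline, week 12 and week 24. Neither it nor the Primary Outcome Measure section names a primary time point.

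The Data Analyses section uses linear mixed models that account for repeated measurement and for clustering, and says that this approach "will provide estimates on the within-group and between-group changes in accelerometer-measured moderate intensity PA", along with the secondary outcomes. After a sentence on sensitivity and exploratory subgroup analyses, it states that "statistical significance for main effects will be assessed at the 5% level". No visit, interaction term or baseline covariate is mentioned.

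**The concern.** When baseline is one of the repeated outcomes, the treatment effect in a mixed model is a group-by-visit contrast. The group main effect is something else. With reference coding and an interaction in the model, it is the difference between groups at baseline, which randomization sets to zero in expectation. Without the interaction, or averaged over visits, it is a mean that includes baseline, where no effect can exist. Neither is the difference in change to week 24 on which the sample size rests. An analyst who follows the sentence literally would test a diluted or irrelevant quantity.

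There is also an efficiency question. The powered and reported quantity is a between-group change. The baseline measurement needed for adjustment is already collected, and using it as a covariate gives a more precise estimate of the same week-24 effect. In a trial of 52 participants allocated by practice, that precision matters.

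**Working it through.** **Inputs from the Sample Size section.** Difference 11 min/day; SD 12.7 min/day, stated for baseline; power 80%; significance level 5%, taken as two-sided because the side is not stated; 21 per group.

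**Assumed, because the article gives no figure.** Correlation ρ between visits, shown at 0.3, 0.5 and 0.7; equal SD and equal correlation at all visits; equal baseline means; no clustering.

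**1. Reproduce the stated figure.** n per group = 2 × (1.960 + 0.842)² × 12.7² / 11² = 2 × 7.85 × 161.29 / 121 = 20.9, so 21 per group and 42 in total. This matches exactly. The formula is an unadjusted two-sample comparison with the baseline SD standing in for the SD of change. Since SD of change = 12.7 × √(2(1 − ρ)), the two are equal only at ρ = 0.5. Power at 21 per group is 80.1% by the normal approximation and 78.2% by the noncentral t distribution. The t version is used below.

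**2. Literal group main effect, averaged over three visits.** Expected effect = (0 + week-12 effect + 11) / 3. SD of a participant's three-visit mean = 12.7 × √((1 + 2ρ)/3), which is 10.37 at ρ = 0.5.

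| Week-12 effect (min/day) | Averaged effect (min/day) | Power at ρ = 0.5 |
|---|---|---|
| 0 | 3.67 | 20.1% |
| 5.5 | 5.50 | 38.9% |
| 11 | 7.33 | 60.9% |

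The comparator is 78.2% for the week-24 change contrast. Over ρ from 0.3 to 0.7 the main-effect power runs from 17.5% (ρ = 0.7, no week-12 effect) to 70.5% (ρ = 0.3, full week-12 effect).

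**3. Change contrast against baseline-adjusted contrast at week 24.** SD of change = 12.7 × √(2(1 − ρ)). Adjusted residual SD = 12.7 × √(1 − ρ²). The variance of the adjusted contrast relative to the change contrast is (1 − ρ²) / (2(1 − ρ)) = (1 + ρ)/2.

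| ρ | SD change | SD adjusted | Variance reduction | Power at 21 per group: change / adjusted | n per group for 80%: change / adjusted |
|---|---|---|---|---|---|
| 0.3 | 15.03 | 12.12 | 35% | 63.9% / 81.9% | 31 / 21 |
| 0.5 | 12.70 | 11.00 | 25% | 78.2% / 88.5% | 22 / 17 |
| 0.7 | 9.84 | 9.07 | 15% | 94.2% / 97.0% | 14 / 12 |

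The single degree of freedom spent on the covariate is ignored. Clustering by practice would lower every power figure in steps 2 and 3.

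**The case against.** The best defence is that the phrase is loose rather than wrong. It follows directly on the exploratory subgroups, so it may simply mean the main comparisons. The same paragraph names between-group changes as the target, which in a repeated-measures model is already a group-by-visit quantity, and the cost analysis uses a difference-in-difference. A separate analysis plan may settle the model. This stands as far as it goes: the article does not prove that the wrong term will be tested. But even on the generous reading, the sentence does not say which visit or which contrast carries the 5% test, and in a mixed-model paragraph the phrase has a technical meaning that an analyst could follow.

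A between-group change is also a valid estimator under randomization, and the gain from adjustment is small when ρ is high. Both points are correct. The article does not rule out a baseline covariate, and a mixed model with a common baseline mean could recover most of the precision. The loss is therefore possible, not shown.

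Three stronger readings are tempting and should not be drawn:

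- *That the trial is powered on a baseline-adjusted contrast which the analysis then abandons.* The Sample Size section describes an unadjusted change, and 42 reproduces from an unadjusted formula.
- *That weeks 12 and 24 are both tested as primary at 5%.* Such a rule would give a familywise error of about 7.8% to 9.1% for contrast correlations of 0.8 to 0.5, but the article states no such rule.
- *That the mixed-model tests will be too liberal with few practices.* The number of practices, the intraclass correlation, the estimation method and the degrees-of-freedom method are not given, so no error rate can be attached to this plan.

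**Conclusion.** The point holds as a badly fixed testing sentence together with a free gain in precision. The 5% test is not tied to the contrast that justifies the sample size. If the sentence is followed literally as a three-visit group main effect, 11 min/day becomes 3.7 to 7.3 min/day and power falls from 78% to about 20% to 61% at ρ = 0.5. Whether that would happen depends on how the phrase is read.

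Adjusting the week-24 contrast for baseline PA would cut its variance by 35%, 25% or 15% at ρ = 0.3, 0.5 or 0.7, and would make power depend less on a correlation that the article does not give. This is an efficiency recommendation; it does not correct any mismatch with the power calculation. All the power figures assume 21 analysed per group, equal variances and correlations across visits, and no clustering.

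**What to change.** Replace the reference to main effects with one primary test: the between-group difference in self-managed moderate intensity PA at week 24, taken from the group-by-visit term, with baseline PA as a covariate and a random effect for practice, at the two-sided 5% level. State that the week-12 difference is secondary.

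As an option, specify restricted maximum likelihood with a small-sample degrees-of-freedom correction. This is prudent if few practices take part, and would give somewhat wider intervals.

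The change costs wording only. It needs no new measurement, because baseline PA is already collected, and the Results section reports that participant recruitment had not begun, so at that stage it could be made before any outcome data existed.
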